#### ■ 30-day postoperative complications

#### ■ 30-day postoperative mortality

#### ■ 3-year and 5-year OS rates (calculated 3 and 5 years after the last participant is enrolled)

#### ■ Locoregional recurrence rate

### **7.3 Other pre-specified outcome measures**

#### ■ Operative outcomes:

1) Operation time (min)

2) Estimated blood loss (ml)

3) Conversion to open surgery (only applicable to the laparoscopic resection group)

4) Events of intraoperative complications

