### 8.3.3 Outcome analysis

- **Analysis of primary outcome measures**

The DFS is calculated using the Kaplan-Meier method after the last participant has been enrolled for three years. The median DFS time and its 95% confidence interval are compared between the two groups using the log-rank test. Cox regression is used to calculate the hazard ratio and its one-sided 95% confidence interval between the two groups. According to the prespecified noninferiority criteria, the inferiority of the treatment to be tested compared with the control treatment is determined.

- **Analysis of secondary outcome and other pre-specified outcome measures**

(1) Pathologic outcomes, including the TME quality, negative CRM, and negative DRM, are presented as numbers (percentage) and compared using the Chi-square test.

(2) The operation time (min) and estimated blood loss (ml) are compared between the groups by the Wilcoxon method.

(3) The OS is calculated using the Kaplan-Meier method after the last participant has been enrolled for three years. The median OS time and its 95% confidence interval are compared between the two groups using the log-rank test.

(4) The OS when the last participant is enrolled for five years is determined by using the Kaplan-Meier method. The median OS time and its 95% confidence interval are compared between the two groups using the log-rank test.

(5) Time to tumor recurrence is determined using the Kaplan-Meier method. The median time of recurrence and its 95% confidence interval are compared between the two groups using the log-rank test.

(6) The perioperative recovery time is compared between the groups using the Wilcoxon method.

(7) The length of postoperative hospital stay (d) is compared between the groups using the Wilcoxon method.

(8) The incidence of intraoperative complications is compared between the groups by the  $\chi^2$  test or Fisher's exact probability method.

(9) After surgery, the incidence of complications and 30-day mortality rate are compared using the  $\chi^2$  test or the Fisher's exact tests for probability.

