**Table 10. The OS (mon) for Laparoscopic Surgery vs Open Surgery within 3 Years after Surgery(mITT)**

|                    | Laparoscopic Surgery Group | Open Surgery Group | P value |
|--------------------|-----------------------------------|---------------------------|-----------------------|
| N           | XXX                               | XXX                       | X.XXX                 |
| Censored(%) | XX(XX.X)                          | XX(XX.X)                  |                       |
| Events(%)   | XX(XX.X)                          | XX(XX.X)                  |                       |
| 25%(95%CI)  | XX.X (XX.X~XX.X)                  | XX.X (XX.X~XX.X)          |                       |
| 50%(95%CI)  | XX.X (XX.X~XX.X)                  | XX.X (XX.X~XX.X)          |                       |
| 75%(95%CI)  | XX.X (XX.X~XX.X)                  | XX.X (XX.X~XX.X)          |                       |

**Figure 3.** Kaplan–Meier curve for comparison of 3-year overall survival rate between two groups (mITT)

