**Table 11. The OS (mon) for Laparoscopic Surgery vs Open Surgery within 5 Years after Surgery(mITT)**

|                    | Laparoscopic Surgery Group | Open Surgery Group | P value |
|--------------------|-----------------------------------|---------------------------|-----------------------|
| N           | XXX                               | XXX                       | X.XXX                 |
| Censored(%) | XX(XX.X)                          | XX(XX.X)                  |                       |
| Events(%)   | XX(XX.X)                          | XX(XX.X)                  |                       |
| 25%(95%CI)  | XX.X (XX.X~XX.X)                  | XX.X (XX.X~XX.X)          |                       |
| 50%(95%CI)  | XX.X (XX.X~XX.X)                  | XX.X (XX.X~XX.X)          |                       |
| 75%(95%CI)  | XX.X (XX.X~XX.X)                  | XX.X (XX.X~XX.X)          |                       |

**Figure 4.** Kaplan–Meier curve for comparison of 5-year overall survival rate between two groups (mITT)

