**Table 12. Time to Tumor Recurrence (mon) (mITT)**

|                    | Laparoscopic Surgery Group | Open Surgery Group | P value |
|--------------------|-----------------------------------|---------------------------|-----------------------|
| N           | XXX                               | XXX                       | X.XXX                 |
| Censored(%) | XX(XX.X)                          | XX(XX.X)                  |                       |
| Events(%)   | XX(XX.X)                          | XX(XX.X)                  |                       |
| 25%(95%CI)  | XX.X (XX.X~XX.X)                  | XX.X (XX.X~XX.X)          |                       |
| 50%(95%CI)  | XX.X (XX.X~XX.X)                  | XX.X (XX.X~XX.X)          |                       |
| 75%(95%CI)  | XX.X (XX.X~XX.X)                  | XX.X (XX.X~XX.X)          |                       |

**Figure 5.** Kaplan–Meier curve for comparison of tumor recurrence rate between two groups (mITT)

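### The secondary endpoints are 3-year and 5-year OS rates, but the SAP compares median OS and specifies no numeric rate with CI, no difference and no hazard ratio

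*Combined protocol and SAP*

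**What the plan says.** **Endpoint.** SAP 7.2 and protocol 8.2 list the same secondary endpoint: "3-year and 5-year OS rates (calculated 3 and 5 years after the last participant is enrolled". It is a survival proportion at two fixed times.

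**Analysis.** SAP 8.3.3, secondary outcomes, item (3) begins: "The OS is calculated using the Kaplan-Meier method after the last participant has been enrolled for three years". It continues: "The median OS time and its 95% confidence interval are compared between the two groups using the log-rank test". Item (4) repeats this for the five-year look, and protocol 12.2 (3) has the same text.

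**Outputs.** SAP Table 10 is titled "The OS (mon) for Laparoscopic Surgery vs Open Surgery within 3 Years after Surgery(mITT" and Table 11 "The OS (mon) for Laparoscopic Surgery vs Open Surgery within 5 Years after Surgery(mITT". Each has rows for N, censored, events and the 25%, 50% and 75% quantiles in months with CIs, plus a P value. Beneath them, Figure 3 is captioned "Kaplan–Meier curve for comparison of 3-year overall survival rate between two groups (mITT" and Figure 4 "Kaplan–Meier curve for comparison of 5-year overall survival rate between two groups (mITT".

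**Elsewhere in the SAP.** DFS gets a Cox hazard ratio with CI (8.3.3 and Table 9). Pathologic outcomes and complications have a column for the difference with 95% CI (Tables 5 and 6). OS has neither.

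**The concern.** The endpoint and its summary measure do not match. A median is a time and a 3-year rate is a proportion. The log-rank test compares whole curves and estimates neither.

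The stated objective is long-term efficacy compared with open surgery. If the median lies beyond the data, the quantile rows of the OS tables will be largely empty, leaving event counts, a curve and a difference-test P value. From those a reader cannot tell how large a survival difference the data are compatible with, in either direction.

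**Working it through.** **Plan figures available.** The documents state no OS rate, OS power or OS precision, so there is no OS figure to reproduce. The inputs below come from SAP 8.1 and protocol 5:

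- assumed control 3-year DFS: 94.3% (stage I) and 75.2% (stage II/III);
- patients by stage: 359 + 609 = 968;
- patients by arm: 646 laparoscopic + 322 open = 968;
- margin: 10 points on 3-year DFS;
- dropout allowance: 20%.

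How 968 was derived does not bear on this point; the arm sizes are taken as given.

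**Step 1: why DFS is a floor for OS.** Death is a DFS event. OS runs from randomization and DFS from surgery (protocol 8.4.1 and 8.4.2). A patient's OS time is therefore never shorter than the DFS time, and OS at any t is at least DFS at that t.

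**Step 2: floor over time.** Assume exponential survival within stage, S(t) = S(3)^(t/3), mixed 359:609:

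floor(t) = [359 × 0.943^(t/3) + 609 × 0.752^(t/3)] / 968

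At t = 3: (359 × 0.943 + 609 × 0.752) / 968 = 0.823. For an arm exactly at the margin, replace 0.943 by 0.843 and 0.752 by 0.652.

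| Floor for OS | 3 y | 5 y | 8 y | Median |
|---|---|---|---|---|
| Control mix | 82.3% | 72.8% | 61.1% | 11.8 y |
| Arm at the margin, mix | 72.3% | 58.7% | 43.6% | 6.6 y |

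By stage, the control median is 3 × ln(0.5)/ln(S(3)): 7.3 years for stage II/III and 35.4 years for stage I.

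**Step 3: what Tables 10 and 11 would show.** Both mixed medians lie beyond 3 and 5 years, so the 50% row is not expected to be filled in either table, even for an arm at the margin. The 75% row comes later still. In the control arm the floor at 3 years (82.3%) is above 75%, so the 25% row of Table 10 is not expected to be filled either.

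**Step 4: what the missing estimate would deliver.** The 95% half-width for a difference in rates, with the same true rate S in both arms, is 1.96 × √[S(1−S)(1/n_L + 1/n_O)]. At S = 0.80 with 646 vs 322: 1.96 × √[0.16 × (1/646 + 1/322)] = 5.35 points. With 20% lost, 0.8 × 646 ≈ 517 and 0.8 × 322 ≈ 258.

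| Assumed true OS, both arms | 646 vs 322 | 517 vs 258 |
|---|---|---|
| 80% | ±5.35 | ±5.98 |
| 85% | ±4.77 | ±5.33 |
| 90% | ±4.01 | ±4.48 |
| 95% | ±2.91 | ±3.26 |

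The OS rates here are assumptions. The second column is a rough allowance for censoring, which the Greenwood variance would handle properly.

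**The case against.** **The rates are estimated after all.** A reader might infer that the 3-year and 5-year rates are never estimated. The documents do not support that. The endpoint says the rates are calculated, Kaplan-Meier is the estimator of survival at 36 and 60 months, and Figures 3 and 4 are captioned as comparing those rates. What stands is narrower: no number, CI or between-arm contrast is named.

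**The median might be reached.** Saying it cannot be reached is also too strong. The floor rests on DFS and an exponential curve beyond the only stated time point. Tables 10 and 11 are limited by title to 3 and 5 years, but the accrual and follow-up wording is ambiguous. If the earliest patients were followed for 8 years (3 years of accrual plus 5), the floor in an arm at the margin would be 43.6%, which no longer excludes a median.

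**The log-rank test is valid, and the shells are only proposed.** Both are true. The log-rank test is a conventional comparison for a secondary survival endpoint, and the shells do not prevent the rates from being printed from the same output. But following the plan as written still leads with a summary that is not the endpoint.

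**No margin is set for OS.** The 10-point margin belongs to 3-year DFS, so OS need not be tested for noninferiority. Nor does any passage say that a P value above 0.05 will be read as equivalence. The case for an interval rests on estimating the stated endpoint, not on a predicted misreading.

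**Table 12.** A reader might extend the point to the table titled "Time to Tumor Recurrence (mon) (mITT", which has the same layout. The listed recurrence endpoint is a locoregional rate with no 3-year or 5-year time point, so this argument does not carry over.

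**Conclusion.** The mismatch is real and plain from the text: the endpoints are fixed-time OS rates, while the prescribed comparison is of medians. No numeric rate with CI, difference with CI or hazard ratio with CI is specified for OS.

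On the plan's own DFS assumptions, median OS is not expected within 3 or 5 years. That conclusion depends on DFS as a floor, exponential survival within stage and the planned stage mix. It also holds for an arm that loses the full 10 points of DFS in each stage.

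The point concerns a secondary endpoint. It does not affect the primary analysis or the validity of the log-rank test.

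**What to change.** In SAP 8.3.3 items (3) and (4), the matching text of protocol 12.2 (3), and SAP Tables 10 and 11:

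- replace the comparison of medians with Kaplan-Meier OS rates at 36 and 60 months per arm, each with a 95% CI using Greenwood's variance;
- add the laparoscopic-minus-open difference at each time with a two-sided 95% CI;
- keep the log-rank test as supportive;
- optionally add a Cox hazard ratio with 95% CI, since a Cox model is already planned for DFS;
- state the time origin for the 36 and 60 months, because protocol 8.4.2 counts OS from randomization while the table titles count from surgery.

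The cost is SAP and protocol wording and two table shells. No new data, visits or patients are needed.

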### 8.3.4 Safety analysis

(1) The incidences of adverse events and adverse reactions are calculated.

(2) The frequency and number of adverse events and reactions will be presented by system organ class and preferred term (MedDRA).

#### **8.4 Statistical software and general requirements**

(1) SAS 9.4 is used for analysis (SAS Institute Inc., Cary, NC, USA).

(2) Generally, two-sided tests are used for statistical analysis, and a  $P$  value  $< 0.05$  indicates that the difference is statistically significant.

### **9 Proposed format of statistical results in the publication of the main results**

**Table 1. Summary of Analysis Population All Subjects Randomized**

|                                | Laparoscopic Surgery
Group | Open Surgery Group | Total |
|--------------------------------|---------------------------------------|---------------------------|--------------|
| Enrollment
subjects | XXX                                   | XXX                       | XXX          |
| Complete subjects       | XXX                                   | XXX                       | XXX          |
| mITT subjects           | XXX                                   | XXX                       | XXX          |
| PPS subjects            | XXX                                   | XXX                       | XXX          |
| SS subjects             | XXX                                   | XXX                       | XXX          |

**Table 2. List of cases not included in mITT (enrolled subjects)**

| Group | Center | Random
number | Clinical
stage | Reason | mITT | PPS | SS |
|--------------|---------------|--------------------------|---------------------------|---------------|-------------|------------|-----------|
| XXX          | XXX           | XXX                      | XXX                       | XXX           | XXX         | XXX        | XXX       |
| ...          | ...           | ...                      | ...                       | ...           | ...         | ...        | ...       |
| ...          | ...           | ...                      | ...                       | ...           | ...         | ...        | ...       |
| ...          | ...           | ...                      | ...                       | ...           | ...         | ...        | ...       |
| XXX          | XXX           | XXX                      | XXX                       | XXX           | XXX         | XXX        | XXX       |

**Table 3. Demographic and Baseline Characteristics**

| Characteristics                                     | Laparoscopic Surgery Group (n=XXX) | Open Surgery Group (n=XXX) | P value |
|------------------------------------------------------------|-------------------------------------------|-----------------------------------|----------------|
| Male, n (%)                                         | XXX(XX.X)                                 | XXX(XX.X)                         | X.XXX          |
| Age, median (IQR), year                             | XXX (XX.X–XX.X)                           | XX (XX.X–XX.X)                    | X.XXX          |
| BMI, median (IQR), kg/m^2                 | XX (XX.X–XX.X)                            | XX (XX.X–XX.X)                    | X.XXX          |
| BMI <25.0 kg/m  , n (%)                        | XXX(XX.X)                                 | XXX(XX.X)                         | X.XXX          |
| 25.0 kg/m  ≤BMI<30.0 kg/m  , n (%) | XXX(XX.X)                                 | XXX(XX.X)                         | X.XXX          |
| BMI≥30.0 kg/m  , n (%)                         | XXX(XX.X)                                 | XXX(XX.X)                         |                |
| ECOG score, n (%)                                   |                                           |                                   | X.XXX          |
| 0                                                          | XXX(XX.X)                                 | XXX(XX.X)                         |                |
| 1                                                          | XXX(XX.X)                                 | XXX(XX.X)                         |                |
| 2                                                          | XXX(XX.X)                                 | XXX(XX.X)                         |                |
| ASA score, n (%)                                    |                                           |                                   | X.XXX          |
| I                                                          | XXX(XX.X)                                 | XXX(XX.X)                         |                |
| II                                                         | XXX(XX.X)                                 | XXX(XX.X)                         |                |
| III                                                        | XXX(XX.X)                                 | XXX(XX.X)                         |                |
| Comorbidity, n (%)                                  |                                           |                                   | X.XXX          |
| Yes                                                        | XXX(XX.X)                                 | XXX(XX.X)                         |                |
| No                                                         | XXX(XX.X)                                 | XXX(XX.X)                         |                |
| Tumor distance from dentate line, median (IQR), mm  | XX (XX.X–XX.X)                            | XX (XX.X–XX.X)                    | X.XXX          |
| Clinical TNM stage, n (%)                           |                                           |                                   | X.XXX          |
| I                                                          | XXX(XX.X)                                 | XXX(XX.X)                         |                |
| II/III                                                     | XXX(XX.X)                                 | XXX(XX.X)                         |                |
| Preoperative therapy, n (%)                         |                                           |                                   | X.XXX          |
| Chemoradiotherapy                                          | XXX(XX.X)                                 | XXX(XX.X)                         |                |
| Radiotherapy alone                                         | XXX(XX.X)                                 | XXX(XX.X)                         |                |
| Chemotherapy alone                                         | XXX(XX.X)                                 | XXX(XX.X)                         |                |
| Without Chemoradiotherapy                                  | XXX(XX.X)                                 | XXX(XX.X)                         |                |

**Table 4. Surgical Details**

| Characteristics                        | Laparoscopic Surgery Group
(n=XXX) | Open Surgery Group
(n=XXX) | P value |
|-----------------------------------------------|-----------------------------------------------|---------------------------------------|----------------|
| Conversion to open resection, n (%)    | XXX(XX.X)                                     | -                                     | -              |
| Operative time, median (IQR), min      | XX (XX.X–XX.X)                                | XX (XX.X–XX.X)                        | X.XXX          |
| Combined resection, n (%)              | XXX(XX.X)                                     | XXX(XX.X)                             |                |
| Uterus                                        | X                                             | X                                     |                |
| Ovaries                                       | X                                             | X                                     |                |
| Seminal vesicle                               | X                                             | X                                     |                |
| Vagina                                        | X                                             | X                                     |                |
| Bladder                                       | X                                             | X                                     |                |
| ...                                           | X                                             | X                                     |                |
| ...                                           | X                                             | X                                     |                |
| ...                                           | X                                             | X                                     |                |
| Estimated blood loss, median (IQR), mL | XX (XX.X–XX.X)                                | XX (XX.X–XX.X)                        | X.XXX          |
| Intraoperative complications No. (%)   | XXX(XX.X)                                     | XXX(XX.X)                             | X.XXX          |
| Bleeding                                      | XXX(XX.X)                                     | XXX(XX.X)                             |                |
| Presacral hemorrhage                          | XXX(XX.X)                                     | XXX(XX.X)                             |                |
| Rectum perforation                            | XXX(XX.X)                                     | XXX(XX.X)                             |                |
| Urinary tract injury                          | XXX(XX.X)                                     | XXX(XX.X)                             |                |
| ...                                           | XXX(XX.X)                                     | XXX(XX.X)                             |                |
| ...                                           | XXX(XX.X)                                     | XXX(XX.X)                             |                |
| ...                                           | XXX(XX.X)                                     | XXX(XX.X)                             |                |
| Type of surgery, n (%)                 |                                               |                                       | X.XXX          |
| LAR                                           | XXX(XX.X)                                     | XXX(XX.X)                             |                |
| ISR                                           | XXX(XX.X)                                     | XXX(XX.X)                             |                |
| APR                                           | XXX(XX.X)                                     | XXX(XX.X)                             |                |
| Others                                        | XXX(XX.X)                                     | XXX(XX.X)                             |                |
| Sphincter preserving, n (%)            | XXX(XX.X)                                     | XXX(XX.X)                             | X.XXX          |
| Diverting ostomy, n (%)                |                                               |                                       | X.XXX          |
| Yes                                           | XXX(XX.X)                                     | XXX(XX.X)                             |                |
| No                                            | XXX(XX.X)                                     | XXX(XX.X)                             |                |

